### Adverse Events and Risk Management

There are some potential risks to participants, such as escalation of violence, as they reside at the same household as the perpetrator. Participants will be briefed about safety behaviors and contact numbers of local authorities and the study team (ie, health care providers, psychiatrists) that they may seek help from when in need. If any participants are in grave danger and do not want to go home, they will be referred to local shelter homes managed by different community organizations and NGOs.

If any other unprecedented harm or risk arises affecting the involved participants in any study arm, data collectors and intervention implementers from each site will notify the project coordinator immediately and manage the situation per guidance from the study team, depending upon the intensity of the adverse event. Adverse events would include a marked increase in suicidal thoughts, the death of the participants, suicide attempts, serious violence, the need for prolonged hospitalization, disability/incapacity, and any other life-threatening events. The study team will also assess these factors throughout the study period.

Any participant who is at risk for severe injury or who displays severe psychological distress and needs help from a specialist will be referred to a psychiatrist by the study team. Intervention implementers will receive the necessary help and guidance from the study team for risk management at respective sites. If any adverse event is reported by a participant or observed at any stage of the study by the data collector or intervention implementer, the study team will record all the necessary details in an adverse reporting form. This form, which is designed by integrating the adverse event form developed by WHO and the National Institutes of Health (NIH), will be used to capture adverse event details of individual participants throughout the study [25].

### Outcomes Measures

#### Primary Outcomes

The primary outcomes are psychological distress and the frequency and intensity of IPV/domestic violence. IPV/domestic violence will be assessed using the modified WHO multicountry questionnaire [36]. This instrument synthesizes women's experience of physical, sexual, and psychological violence, as well as controlling behavior by husbands/male partners, and also measures the severity of IPV/domestic violence. Psychological distress will be measured with the GHQ-12 [35] and the 9-item Patient Health Questionnaire (PHQ-9) [37]. Both tools have been translated and clinically validated in Nepal. The GHQ-12 has a cut-off score of 0.5, with sensitivity 85.6%, specificity 75.8%, positive predictive value 86.7%, and negative predictive value 84% [38]. Similarly, the PHQ-9 has a cut off score of ≥10, with sensitivity 94%, specificity 80%, positive predictive value 42%, and negative predictive value 99% [39].

#### Secondary Outcomes

The secondary outcomes are safety planning, use of community resources, social support, impaired functioning, symptoms of PTSD, personally identified problems, and health service use. Health care providers’ capacity to identify IPV/domestic violence to provide women experiencing IPV/domestic violence with risk mitigation services will also be assessed. Details of instruments and assessments for primary and secondary outcomes, including follow-up time, are provided in Tables 3-5.

**Table 3 table3:** Overview of instruments and assessments for specific objectives concerning women experiencing IPV^a^/domestic violence.

Study objective and tool			Baseline (T_1_)^b^		Follow-up after baseline				
					6 weeks (T_2_)		17 weeks (T_3_)		52 weeks (T_4_)
**Objective 1:** **Assess the feasibility of DeVI^c^ in health care facilities in Nepal by exploring the views of key stakeholders, health care providers, and local women in the community.**									
	Formative assessment (details have been mentioned in the *Formative Assessment and Consultation Workshop* section)	0^d^		0		0		0	
**Objective 4: Measure the effectiveness of DeVI in addressing and resolving psychological distress, reducing the occurrence of IPV, and developing safety strategies for women experiencing IPV.**									
	Husband/male partner/domestic violence assessment	1^e^		1		1		1	
	GHQ-12^f^ [35]	1		1		1		0	
	Hospital Anxiety Depression Scale [40], PHQ-9^g^ [37], PTSD^h^ CheckList – Civilian Version, Multidimensional Scale of Perceived Social Support [41], WHO^i^ Disability Assessment Schedule [42]	1		1		1		0	
	Safety Behavior Checklist, use of community resources	1		1		1		1	

^a^IPV: intimate partner violence.

^b^T: time point.

^c^DeVI: Domestic Violence Intervention.

^d^0: not applicable.

^e^1: applicable.

^f^GHQ-12: 12-item General Health Questionnaire.

^g^PHQ-9: 9-item Patient Health Questionnaire.

^h^PTSD: posttraumatic stress disorder.

^i^WHO: World Health Organization.

**Table 4 table4:** Overview of instruments and assessments for objective 5 (measure the impact of training health care providers on DeVI^a^ on their knowledge, attitudes, skills, and stigma toward IPV^b^ and the social and health-related consequences of IPV) concerning health care providers.

Tools	Pretraining	Posttraining	Follow-up 1 (T_2_)^c^	Follow-ups (T_3_ and T_4_)
Modified PREMIS^d^ [43]	1^e^	1	0^f^	0
MAKS^g^, Social Distance Scale [44], perceived dangerousness of the mental health patients [44]	1	1	0	1
In-depth interviews with health care providers	0	1	1	1

^a^DeVI: Domestic Violence Intervention.

^b^IPV: intimate partner violence.

^c^T: time point.

^d^PREMIS: Physician Readiness to Manage Intimate Partner Violence Survey.

^e^1: applicable.

^f^0: not applicable.

^g^MAKS: Mental Health Knowledge Schedule.

**Table 5 table5:** Overview of instruments and assessments for specific objectives concerning health care providers and women experiencing IPV^a^/domestic violence.

Study objective	Tool	Session						Follow-up	
		1	2	3	4	5	1 (T_2_)^b^		2 (T_3_)
Objective 4: Measure the effectiveness of DeVI^c^ in addressing and resolving psychological distress, reducing the occurrence of IPV, and developing safety strategies for women experiencing IPV.	PSYCHLOPS^d^ [16]	1^e^	1	1	1	1	1		1
Objective 3: Explore participants’ and health care providers’ experiences with DeVI and the opportunities and challenges encountered during implementation.	Process evaluation	0^f^	0	0	0	0	1		1
Objective 3: Explore participants’ and health care providers’ experiences with DeVI and the opportunities and challenges encountered during implementation.	Exit interview of participants	0	0	0	0	1	0		0

^a^IPV: intimate partner violence.

^b^T: time point.

^c^DeVI: Domestic Violence Intervention.

^d^PSYCHLOPS: Psychological Outcome Profiles.

^e^1: applicable.

^f^0: not applicable.

#### Other Outcomes

Health care providers will be asked to respond to questionnaires, such as the modified Physician Readiness to Manage Intimate Partner Violence Survey (PREMIS), the Mental Health Knowledge Schedule (MAKS), the Social Distance Scale, and the perceived dangerousness of mental health patients pre- and posttraining to assess the impact of training on the health care providers’ knowledge and attitude. Further, MAKS and the perceived dangerousness of mental health patients will be assessed during integrated multicomponent supervision (approximately 90 days posttraining). Exit interviews will be conducted among 180 participants by data collectors in the absence of intervention implementers after the completion of all 5 sessions in a separate room by adopting a mixed methods approach. This will help determine changes postintervention and any aspects that need to be changed. This will also help assess the satisfaction and acceptability of DeVI from the participant’s point of view.

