### Study Aim

This study aims to implement and evaluate the feasibility, acceptability, and effectiveness of DeVI in addressing psychological distress and enabling the secondary prevention of violence for women experiencing IPV through a cluster-randomized trial. The program will be delivered through nonspecialist mental health care providers in public health institutions to increase the feasibility and applicability of such interventions in an LMIC setting. The study will be conducted in Madhesh Province, Nepal, which has the highest-reported prevalence of spousal violence/IPV [6].

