### Participants and Recruitment

#### Sample Size

Based on the sample size calculation, a total of 912 eligible women (456, 50%, in each arm) will be included in the study. This sample size for the cluster-randomized trial was calculated considering 80% power to detect 15% absolute risk reduction in the IPV frequency in the intervention arm at a statistical significance level of α<.05 [32]; we estimated a 50% reduction in mental health problems in the PM+ group, as measured with the 12-item General Health Questionnaire (GHQ-12) [33]. The minimum number of clusters required in each arm was 6, which was later increased to 11 to ensure an efficient trial design [34]. The number of clusters was further increased to 12 to account for dropouts at the cluster level [34]. Finally, a total of 24 clusters (12, 50%, intervention and 12, 50%, control clusters) were included, and 38 eligible women from each cluster regardless of the arms will be enrolled in the study.

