**DeVI^c^**						
	Intervention arm only	90 minutes/week for 5 weeks	Intervention implementers	Intervention implementers	To implement the intended intervention in the intervention arm.	N/A
	Intervention arm only	After session 5	Data collectors	Data collectors	To assess participants’ perception toward the intervention.	Exit interview to assess participants’ satisfaction and suggestions

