#### Follow-up Assessments

Follow-up surveys will be conducted at 3 time points: 6 weeks after baseline assessment (ie, 1 week postintervention), 17 weeks after baseline assessment (ie, 12 weeks postintervention), and 52 weeks after baseline assessment (ie, 47 weeks postintervention). The data collection tools for follow-up will be similar to those for baseline assessments. However, in the last follow-up, participants will be asked questions and will be expected to contribute to the assessment of any sustained effects of DeVI on the prevention of revictimization and improvement in coping strategies against IPV. An exit interview will be conducted after intervention session 5.

IDIs will be conducted with health care providers from the intervention arm during or after the intervention to explore their experiences and perspectives of DeVI and program implementation. Health workers will be mobilized to identify suitable participants in the community, and those who provide written informed consent will be contacted for confidential interviews, preferably at the health care facility, both during and after the intervention.

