### Limitations

Women experiencing violence and eligible for our study may refrain from providing consent due to the fear that their husbands or male partners will subject them to further abuse upon discovering their participation. The dropout rate may be higher due to the associated stigma and the fear of family members, society, and perpetrators. In a patriarchal society, such as Nepal, women are typically accompanied by their in-laws or husbands when seeking basic services at health care facilities, which creates reluctance to disclose issues related to violence or participate in the study.

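### The exit interview rates satisfaction and acceptability only in women who finish all five DeVI sessions, so its result is likely to overstate acceptability among all women who start

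*Protocol article*

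**What the plan says.** The Study Aim section names acceptability beside feasibility and effectiveness: "This study aims to implement and evaluate the feasibility, acceptability, and effectiveness of DeVI".

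Four places in the article fix when the exit interview is held, and they agree:

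- Other Outcomes: "Exit interviews will be conducted among 180 participants by data collectors in the absence of intervention implementers after the completion of all 5 sessions".
- Table 2, intervention arm, after session 5: "Exit interview to assess participants’ satisfaction and suggestions".
- Follow-up Assessments: "An exit interview will be conducted after intervention session 5".
- Table 5: the exit interview is marked at session 5 only, with a zero at sessions 1 to 4 and at both listed follow-ups.

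Other Outcomes also gives its purpose: "This will also help assess the satisfaction and acceptability of DeVI from the participant’s point of view".

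The planned enrolment is "a total of 912 eligible women (456, 50%, in each arm) will be included in the study". On retention, the Limitations section says "The dropout rate may be higher due to the associated stigma" and adds fear of family, society and perpetrators. No figure for session completion or dropout is given.

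Three other sources bear on acceptability:

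- Table 2 has female community health volunteers trace women who miss visits in both arms and record why.
- Qualitative Data Collection plans interviews with purposively selected participants and says that the qualitative process assessment will also inform acceptability.
- Process Evaluation includes acceptability among women in its scope, but the interviews it describes are with data collectors and implementers.

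**The concern.** Attending five weekly sessions of about 90 minutes is itself a sign that a woman found the programme tolerable and could attend safely. If satisfaction is asked only after the fifth session, the question goes to a group partly selected on the answer. A woman who left after session 2 because attendance felt unsafe or unhelpful contributes nothing to the satisfaction result.

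The stake is interpretation. Effects on outcomes are to be analysed by intention to treat, so they describe all women enrolled. A satisfaction result from completers, printed beside those effects without its denominator, could be taken to describe the same women. The article treats acceptability as important for scale-up and for integration into routine services, so a reader is likely to use the figure in that way.

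**Working it through.** **1. The number 180.** The article gives no derivation, so it cannot be reproduced. It can be set against the arm size: 12 facilities x 38 women = 456, which agrees with the stated 456 per arm.

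- 180 / 456 = 39.5% of planned intervention women, or 180 / 12 = 15 per site if spread evenly.
- If all 456 start and 60% complete, there are 274 completers and 180 is 66% of them. At 95% completion there are 433, and 180 is 42%.

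No draw of 180 from completers, however made, contains a woman who stopped early.

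**2. Whether another source fills the gap.**

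| Source | Who is covered | Could it give a participant satisfaction proportion for starters? |
|---|---|---|
| Exit interview | Women after session 5 | No, completers only |
| Tracing of women who miss visits | Both arms | No. It records reasons, not satisfaction |
| Purposive interviews | Participants, no completion condition stated | No. Early stoppers need not be included, and a purposive sample gives no proportion |
| Process evaluation interviews | Data collectors and implementers | No |

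Follow-up Assessments also mentions confidential interviews during and after the intervention. The text does not make clear whether these are with women or with providers.

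**3. Size of the bias.** Let c be the share of starters who complete, S_c satisfaction among completers and S_n satisfaction among early stoppers.

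- Among all starters: S = c x S_c + (1 - c) x S_n
- Bias of the completer figure: S_c - S = (1 - c) x (S_c - S_n)

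The documents give none of these inputs. With S_c assumed to be 90%:

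| Completion c | S_n = 90% | S_n = 70% | S_n = 50% | S_n = 30% |
|---|---|---|---|---|
| 95% | 0 | +1 | +2 | +3 |
| 80% | 0 | +4 | +8 | +12 |
| 70% | 0 | +6 | +12 | +18 |
| 60% | 0 | +8 | +16 | +24 |

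Example: 0.8 x 0.9 + 0.2 x 0.5 = 0.82 among all starters, against 0.90 among completers, a bias of 8 points.

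**4. Against sampling error.** For n = 180 and 90% satisfied, ignoring clustering, the 95% half-width is 1.96 x sqrt(0.9 x 0.1 / 180) = 4.4 points. The bias exceeds this when the satisfaction gap is larger than 0.044 / (1 - c): 11 points at 60% completion, 22 points at 80%, and 88 points at 95%. It can therefore be trivial or dominant, depending mainly on completion.

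**The case against.** The strongest reply is that the exit interview is not the whole acceptability assessment. The article says only that it helps. Purposive interviews with participants carry no completion condition, and it is the qualitative process assessment that the article ties directly to scale-up. Reasons for non-attendance are recorded as well. This stands, and it rules out reading the plan as measuring acceptability solely in completers. It does not supply what is missing, because none of these sources must include early stoppers' satisfaction and none yields a proportion.

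Four further inferences are tempting but unsupported:

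- That the result will be too favourable. Upward is the plausible direction, but a woman kept away by her family may be quite satisfied with DeVI, and with no gap the bias is zero.
- That the 180 are not drawn at random. The article states no selection rule, and an article commonly leaves that to the full protocol.
- That the protocol expects women to leave because they find DeVI unacceptable. It speaks of stigma and fear, which bear on safety but are not a judgement of the programme.
- That reasons for non-attendance are kept out of the acceptability assessment. The article does not say how the sources will be combined.

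It is also fair to say that feedback on the whole package needs women who have seen the whole package. That justifies interviewing completers, but not omitting everyone else.

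**Conclusion.** The point holds in a limited form. The only described participant measure of satisfaction, and the only described source that could give a participant acceptability figure, is conditional on finishing all five sessions. Four consistent statements make this the plan rather than loose wording. The figure is likely to overstate acceptability among all women who start DeVI.

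The amount cannot be fixed from the documents. The range of 0 to 24 points rests entirely on assumed completion of 60% to 95%, assumed satisfaction of 90% in completers and 30% to 90% in early stoppers. A reader might infer that the trial's main conclusions are at risk. They are not: the exit interview sits under Other Outcomes, and the primary and secondary outcomes, the intention-to-treat analysis and the sample size of 912 do not depend on it. This is a worthwhile, inexpensive improvement.

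**What to change.** For women who attended at least one session but stopped before session 5, have the data collector give the same exit form at the existing 6-week visit, where safe contact is possible under the retention procedures already described.

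Report satisfaction and acceptability over all starters interviewed, with completers shown separately. Beside it, give the numbers starting, completing and not reached, and the recorded reasons for non-attendance. Because only 180 completers are interviewed, combine the two groups by their observed shares among starters rather than by pooling interviews. In the 80% completion example, with all 456 starting and all 91 early stoppers interviewed, simple pooling gives (180 x 0.9 + 91 x 0.5) / 271 = 77%, against the correct 82%.

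Cost: no new visit and no new staff, since data collectors already run both the exit interviews and the 6-week visits. There is added interview time, for between 5% and 40% of 456 women (about 23 to 182) under the completion rates assumed above.

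Downsides:

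- Some early stoppers will not be reached, so part of the selection remains.
- Women already past their 6-week visit cannot be included in this way, and 269 of 456 intervention women (59%) had been enrolled by 29 December 2022.
- The reported acceptability may be lower.

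At the least, label the exit-interview results as completers' views and print the attendance numbers with them.

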### Quantitative Data Collection for the Trial

Quantitative data will be collected electronically using REDCap software [45] and various data collection tools by data collectors in computer-based tablets at different time points. If any technical problem arises during electronic data collection, paper-based data collection will be performed. Each health care facility will be provided with a computer-based tablet with an updated questionnaire for data collection.

Data collection tools will include structured surveys and standard validated tools. The structured surveys will include questions on participants’ personal information (date of birth, ethnicity, address, contact information, and preferred time to call) and sociodemographic characteristics. The data collection tools in this study are standard international tools widely used and validated in different countries. However, some terminologies and contents have been contextualized to suit the Nepali context. The data will be collected at 4 different time points, once at baseline and at 3 follow-up time points (see Figure 3 for details). In addition, the PSYCHLOPS form will be filled in at the 5 intervention sessions.

### Qualitative Data Collection

Qualitative interviews will be conducted by purposively selecting participants to learn more about their perspectives toward DeVI. IDIs will be conducted with randomly selected intervention implementers to understand their challenges in implementing the intervention sessions and their suggestions for improving the applicability and sustainability of DeVI. A deeper understanding of their needs will help the study team alter the intervention approach and activities in the future. The qualitative process assessment will also help assess the acceptability of DeVI, which is key for scale-up and integration into routine services.

### Data Management and Analysis

#### Quantitative Data Analysis

Electronically collected data will be securely stored in a central office cloud, accessible only to designated study team members. Paper-based data pertaining to the study will be secured in a locker and retrieved from data collectors during central study team monitoring. Regular checks will be conducted to ensure data accuracy and quality, with necessary feedback provided to the data collectors. The primary measure of intervention effects will be based on intention-to-treat analyses. Multilevel analysis will be conducted to account for DeVI’s impact on primary and secondary outcomes, adjusting for clustering at the health center level [46]. The model will consider intervention × time interactions to assess the differential effects of DeVI on changes in outcomes from baseline to the final follow-up. Cluster-level variables will also be compared between intervention and control arms since randomization is based on health care facilities. Furthermore, the study will assess variations in outcome measures of interest between urban and rural areas.

The knowledge, perception, and preparedness of both intervention implementers and data collectors will be assessed before and after the training through pre-, post-, and follow-up tests. Quantitative data will be analyzed using STATA 15 software.

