**Methods:**

A parallel cluster-randomized trial will be conducted across 8 districts in Madhesh Province in Nepal, involving 24 health care facilities. The study will include women aged 18-49 years who are either nonpregnant or in their first trimester, have experienced IPV within the past 12 months, have a 12-item General Health Questionnaire (GHQ-12) score of 3 or more (indicating current mental health issues), and have lived with their husbands or in-laws for at least 6 months. A total sample size of 912 was estimated at 80% power and α<.05 statistical significance level to detect a 15% absolute risk reduction in the IPV frequency and a 50% reduction in the GHQ-12 score in the intervention arm. The health care facilities will be randomly assigned to either the intervention or the control arm in a 1:1 ratio. Women visiting the health care facilities in the intervention and control arms will be recruited into the respective arms. In total, 38 participants from each health care facility will be included in the trial to meet the desired sample size. Eligible participants allocated to either arm will be assessed at baseline and follow-up visits after 6, 17, and 52 weeks after baseline.

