#### Eligibility and Screening

The inclusion criteria for the participants are as follows: (1) women aged 18-49 years; (2) those self-reporting experience of abuse (physical, sexual, or psychological) in a heterosexual relationship, involving their husbands/male partners or other family members, occurring within the past 12 months; (3) women who are nonpregnant or in the first trimester; (4) those with a minimum score of ≥3 on the Psychological Distress Scale (measured with sthe GHQ-12) [35]; and (5) those living with their husbands or in-laws for at least 6 months. Women will be excluded if they (1) have severe cognitive impairment, (2) are seeking treatment for life-threatening emergency care, (3) or are at imminent risk for suicidal ideation and attempt. A questionnaire that helps in determining these eligibility criteria will be formulated and used specifically for the purpose of screening women for eligibility. Women who are at imminent risk for suicidal ideation and attempt will be referred to a psychiatrist.

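### For yes/no violence or distress, the planned change-from-baseline interaction is undefined or redundant, because eligibility makes every woman positive at baseline; for scores it is less precise than baseline adjustment

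*Protocol article*

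**What the plan says.** **Analysis.** The Quantitative Data Analysis section describes a multilevel model "adjusting for clustering at the health center level [46]. The model will consider intervention × time interactions to assess" how the intervention changes outcomes between baseline and the final follow-up. It names no link function and no outcome scale.

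**Sample size.** The target is a "15% absolute risk reduction in the IPV frequency in the intervention arm", and for distress "we estimated a 50% reduction in mental health problems in the PM+ group". The Abstract gives the second target as a halving of the GHQ-12 score instead.

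**Outcome.** "The primary outcomes are psychological distress and the frequency and intensity of IPV/domestic violence". The violence instrument is a modified WHO questionnaire, and distress is measured with the GHQ-12 and PHQ-9. The article gives no recall window for the violence instrument.

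**Eligibility.** Women must report abuse "involving their husbands/male partners or other family members, occurring within the past 12 months", and only "those with a minimum score of ≥3 on the Psychological Distress Scale" enter.

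**Follow-up.** Visits are at 6, 17 and 52 weeks. "The data collection tools for follow-up will be similar to those for baseline assessments". Table 3 schedules the violence assessment at all three visits, but the GHQ-12 and PHQ-9 only at 6 and 17 weeks. For distress, the last visit that can enter the model is therefore week 17.

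**The concern.** Three stated choices do not fit together. The sample size uses a proportion, the outcome section speaks of frequency and intensity, and the model estimates change from a baseline that the entry criteria have fixed.

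A proportion that must be 100% in both arms at baseline cannot vary or differ there. Using it as an outcome time point adds nothing at best, and on the logit scale it leaves the interaction without a finite estimate. At stake is the contrast on which the trial was sized. An analyst who takes the text literally and fits a mixed logistic model to any violence would get a meaningless standard error for that contrast and would have to choose another analysis after seeing the data.

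For scores the stake is precision. For early violence results, the stake is whether the questions refer to time after the intervention began.

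**Working it through.** **1. The plan's own figure.** 24 facilities × 38 women = 912, and 12 × 38 = 456 per arm. The arithmetic agrees. The 80% power cannot be reproduced, because the article gives neither a control-arm risk nor an intracluster correlation (ICC). Assuming a two-sided 5% test and control risks of 0.30 to 0.90, a 15-point reduction needs 100 to 173 women per arm before clustering. Solving 456 = n × (1 + 37 × ICC):
- n = 173: (456/173 − 1)/37 = 0.044
- n = 100: (456/100 − 1)/37 = 0.096

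So 912 is attainable under plausible values. This is the scale of the ICC range used in step 4.

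**2. Yes/no outcome, odds-ratio scale.** At baseline each arm has 456 positives and 0 negatives, so the baseline log odds, log(456/0), is infinite in both arms. The interaction is the difference between arms of (follow-up log odds − baseline log odds), and it has no finite standard error. Simulated data with assumed follow-up risks of 0.70 and 0.55 show this:

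| Fitting iterations | Intercept | SE of interaction |
|---|---|---|
| 10 | 11.6 | 13 |
| 20 | 21.6 | 1,936 |
| 30 | 31.6 | 287,484 |
| 40 | 37.6 | about 4.4 million |

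Any single SE from such a fit only shows where the algorithm stopped. Comparing the arms at follow-up alone in the same data gives a log odds ratio of −0.835 with SE 0.141.

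**3. Yes/no outcome, risk-difference scale.** With p₁ and p₀ the follow-up risks, the interaction is (p₁ − 1) − (p₀ − 1) = p₁ − p₀. For 0.55 and 0.70: (−0.45) − (−0.30) = −0.15, which is the follow-up difference. In the simulated data both are −0.191. The contrast is estimable, but baseline contributes nothing.

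**4. Scores.** Assume equal variances at both times, m = 38 women per facility, ICC ρ, correlation r between a woman's baseline and follow-up scores, and correlation c between a facility's true levels at the two times (taken as 0.8 to 1). The correlation of facility means is

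R = (r + 37ρc) / (1 + 37ρ).

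The change contrast has variance proportional to 2(1 − R). Adjusting for the woman's baseline and its facility mean gives 1 − R². The saving is (1 − R)/2.

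- ρ = 0.01, r = 0.3, c = 0.8: R = (0.3 + 0.296)/1.37 = 0.435, saving 28%.
- ρ = 0.09, r = 0.5, c = 1: R = (0.5 + 3.33)/4.33 = 0.885, saving 6%.

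The other combinations fall between these.

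Adjusting for the woman's own baseline alone is not a safe substitute. In the second case its slope is (0.5 − 0.09)/(1 − 0.09) = 0.451. The variance is then proportional to 1 + 0.451² − 2 × 0.451 × 0.885 = 0.41, against 2(1 − 0.885) = 0.23 for the change contrast. When facility differences are stable, the facility mean has to be in the model.

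**5. Recall window, if 12 months is kept at follow-up.** The share of the window that lies before baseline is:
- 6 weeks: (52 − 6)/52 = 46/52 = 88%
- 17 weeks: (52 − 17)/52 = 35/52 = 67%
- 52 weeks: 0%

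**The case against.** The strongest reply is that the article names no logistic model and no yes/no outcome. Frequency, intensity and GHQ-12 scores vary at baseline, and a linear mixed model on them fits the text and converges. This stands. A reader might infer that the main estimate must fail to converge, and the document does not support that: the failure is confined to a logit analysis of the indicators fixed by eligibility. The 100% also applies to abuse by husband or family taken together, and not necessarily to partner violence alone or to each type of violence. What remains is that the sample size is stated as an absolute risk reduction, and for a yes/no outcome on the eligibility definitions the planned contrast is undefined or redundant.

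A reader might also infer that facility is the only clustering level and that the standard errors are therefore wrong. The text names the facility level without excluding a woman level, and random effects and degrees of freedom may sit in an analysis plan not shown. Any error would also have no fixed direction: under assumed variance components, a facility-only intercept gave type I error from 0.6% to about 16%. That reading is not part of this point.

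It is fair, too, that change versus baseline adjustment is a matter of precision and not of validity. The familiar figure for independent women, a saving of (1 − r)/2 = 25 to 35% at r = 0.5 to 0.3, ignores clustering and overstates the gain here.

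Finally, 12 months is stated as an entry criterion. The outcome tool's window is not given, and the follow-up tools are described only as similar. The recall point is therefore conditional and touches only weeks 6 and 17.

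**Conclusion.** The concern holds in a limited form. For any past-12-month abuse and for GHQ-12 of 3 or more, eligibility fixes baseline at 100%. The planned interaction is then not identified as an odds ratio, and as a risk difference it equals the follow-up difference. This follows from the stated criteria and needs no assumed figure.

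For scores the planned contrast is valid but gives up precision: 6 to 28% of its variance could be removed, given ICC 0.01 to 0.09, within-woman correlation 0.3 to 0.5, stable or fairly stable facility levels (c of 0.8 to 1) and equal variances. None of these values is in the article.

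If the 12-month window is reused, violence at 6 and 17 weeks mostly describes time before baseline (88% and 67%), and only week 52 is clean. If the window is shortened at follow-up instead, change from baseline compares a 12-month frequency with one over a shorter period. Either way, baseline is a poor outcome time point for violence at the early visits.

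**What to change.** State the scale of each primary outcome, and replace the change-from-baseline contrast as follows.

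- **Model.** Use follow-up values only as outcomes, with arm, visit as a categorical factor, and arm × visit.
- **Scores** (violence frequency and intensity, GHQ-12, PHQ-9). Adjust for the woman's baseline score and for its facility mean. The alternative is to keep baseline as an outcome and constrain both arms to a common baseline mean, which assumes that recruitment after facilities were randomised brought in comparable women. For distress, name week 17 as the last visit, or reconcile Table 3 with the analysis text.
- **Yes/no violence.** Report the follow-up risk difference with facility-level inference, which matches the sample-size target. With 24 facilities, a t reference on 22 degrees of freedom is the natural choice.
- **Recall.** State the window of the violence questions at each visit. If it is 12 months, make week 52 the violence endpoint. By 29 December 2022, 269 + 309 = 578 women were enrolled, so the recall wording should not be changed midway without recording which window each woman was asked about.

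The cost is slightly more analysis work. The baseline scores are already collected, and neither recruitment nor sample size changes.
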